## Abstract

**Background:**

Robotic nipple-sparing mastectomy (RNSM) has emerged as a new treatment option for breast cancer and risk-reducing mastectomy (RRM) for women who have a high risk of pathogenic variants. Even though several studies have reported that RNSM is a feasible procedure, some argue that it should only be performed by specialized surgeons, and data on oncologic outcomes and patient-reported outcomes (PROs) are limited. Recently, the United States Food and Drug Administration and several surgeons warned that robotic breast surgery should be performed only by specialized surgeons and recommended that the benefits, risks, and alternatives of all available treatment options be discussed with patients so they can make informed treatment decisions. The Korea Robot-Endoscopy Minimal Access Breast Surgery Study Group (KoREa-BSG) has been established to evaluate, standardize, and teach this state-of-the-art procedure. We have designed a multicenter prospective cohort study entitled Mastectomy with Reconstruction Including Robot Endoscopic Surgery (MARRES) to report surgical, PRO, and oncologic outcomes.

**Methods:**

MARRES is a multi-institution cohort study prospectively collecting data from patients undergoing mastectomy and reconstruction. The patient inclusion criteria are adult women older than 19 with breast cancer or a high risk of breast cancer (patients with *BRCA1/2*, *TP53*, *PALB2* mutations, etc.), who have scheduled therapeutic or RRM and want immediate reconstruction. Surgical outcomes, including pre- and postoperative photos, oncologic outcomes, cost-effectiveness, and PRO, are collected. The primary endpoints are postoperative complication rates within 30 postoperative days and the Clavien-Dindo grade of postoperative complications within 180 postoperative days. The secondary endpoints are 5-year postoperative recurrence-free survival and cancer incidence rate (for those who underwent RRM), patient satisfaction with reconstruction expectations preoperative (baseline) and results within 6 to 12 postoperative months, surgeon satisfaction with postoperative results in 6 postoperative months, and cost-effectiveness of the definitive surgery. Patient recruitment will be completed in April 2025, and the target number of enrolled patients is 2000.

**Discussion:**

This study will provide evidence about the surgical outcomes, oncologic outcomes, and patient satisfaction with RNSM and endoscopic nipple-sparing mastectomy (NSM), compared with conventional NSM.

**Trial registration:**

ClinicalTrials.gov Identifier NCT04585074. Registered April 8, 2020.

## Background

Since Toth and Lappert first described a skin-sparing mastectomy (SSM) procedure, similar oncologic outcomes and better patient satisfaction and quality of life (QOL) have been reported for it compared with conventional mastectomy (CM) [1–3]. Immediate breast reconstruction (IBR) is facilitated by preserving the skin envelope at the time of mastectomy, and the success of SSM has paved the way for nipple-sparing mastectomy (NSM). Because NSM has shown better patient satisfaction and cosmetic results than SSM, with comparable oncologic outcomes, it has become popular [4, 5]. NSM with IBR has become widespread as indications have expanded. Increased *BRCA1/2* genetic testing and public awareness have led to a rise in risk-reducing mastectomy (RRM), and there is increased interest in QOL after mastectomy [6, 7].

In NSM, various kinds of skin incisions can be selected [8–10]. To prevent visible scarring and minimize the incision size, endoscopic NSM (ENSM) was developed more than 20 years ago [11–13]. However, ENSM has several limitations: (1) complex devices are needed, (2) the approaches are difficult for endoscopic devices, especially in the medial part of the breast, and (3) it is labor-intensive for surgeons and assistants, especially for large and ptotic breasts. Therefore, ENSM has been performed only by specialized surgeons in East Asia.

Robots are used for various surgeries, including those for malignant diseases. Since the first reports of robotic nipple-sparing mastectomy (RNSM) by Toesca et al. and Park et al. in Korea, RNSM has been performed in selected patients and *BRCA1/2* carriers [14, 15]. Even though several studies have shown that RNSM is a feasible procedure, it is performed by only a few specialized surgeons [16]. Furthermore, few data have been reported about its oncologic outcomes.

Recently, the United States Food and Drug Administration warned that robotic breast surgery should be performed only by specialized surgeons and recommended that the benefits, risks, and alternatives of all available treatment options be discussed with patients so they could make informed treatment decisions. Previous articles have also recommended that randomized controlled trials be conducted to assess the surgical safety, patient reported outcomes (PROs), and oncologic outcomes of RNSM and thus evaluate its clinical role in treating *BRCA1/2* carriers and patients with breast cancer [17, 18].

The Korea Robot-Endoscopy Minimal Access Breast Surgery Study Group (KoREa-BSG) has been established to evaluate, standardize, and teach this state-of-the-art procedure. Previously, the KoREa-BSG retrospectively analyzed the initial experiences of surgeons and showed that RNSM is technically feasible and reliable, with a short learning curve [19]. Therefore, to obtain a high level of evidence, we designed a multicenter prospective exploratory cohort study entitled Mastectomy with Reconstruction Including Robotic Endoscopic Surgery (MARRES) to collect data on surgical outcomes, PROs, and oncologic outcomes (Protocol serial numbers: KoREa-BSG 03 and KBCSG-23).

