#### Guidelines and reviews for ENSM with IBR

Due to aesthetic concerns about the breast, breast surgery has been developed to satisfy both oncologic safety and cosmetic needs [13]. Endoscopic procedures have been used for various breast surgeries, including augmentation, mastectomy, excision, biopsy, capsulectomy, and reconstruction [32].

Endoscopic-assisted breast surgery (EABS) was introduced in the late 1990s to optimize the aesthetic effects by using a minimal incision in an inconspicuous location for benign breast disease or breast cancer [33]. Previous studies reported excellent patient satisfaction on patient-reported questionnaires after ENSM [34–36]. Additionally, endoscopy could offer better visualization with light handle retractions through a small incision and allow similar oncologic outcomes compared to CNSM [13, 37]. Indications and contraindications for EABS are similar to CNSM. Although ENSM is considered a safe and feasible procedure that leaves a relatively inconspicuous incision in patients with breast cancer [38], endoscopic techniques for breast surgery have not been widely performed because of the technical challenges with using rigid instruments [39].

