### Statistical analyses

We have categorized three study sets: Conventional vs. endoscopic, conventional vs. robotic, and conventional vs. endoscopic and robotic. Additionally, subgroup analyses of a randomized registry trial will be conducted to compare the surgical and oncologic outcomes between the conventional and minimally invasive (endoscopic and robotic) groups. Primary and some secondary outcomes (postoperative complications, the satisfaction of patients and surgeons, and the cost-effectiveness evaluation) and other categorical variables will be examined by the chi-square test or Fisher's exact test. Continuous variables will be examined by t-testing or ANOVA and Mann–Whitney testing or Kruskal–Wallis testing, if needed. The other secondary outcomes (RFS, OS, and cancer incidence rates in 5 years) will be examined using Kaplan–Meier plots and log-rank testing. No imputation will be performed for subjects who have missing data due to dropping out of the study. Data relating to major protocol non-adherence due to patients dropping out of the study will be excluded from the analysis population.

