## Discussion

This study will provide evidence about the surgical outcomes, oncologic outcomes, and patient satisfaction with RNSM and ENSM, compared with CM.

This prospective cohort study has some advantages over previous retrospective studies conducted in a single center or with a single surgeon. The sample size of the study is larger than previously published studies of RNSM. Additionally, our protocol will collect large-scale PRO data about cosmesis after RNSM. The participation of many surgeons from multiple institutions will allow us to observe the effects of different surgeons or institutions on the clinical outcomes of the surgical procedures. In Korea, an increasing number of breast surgeons has been performing RNSM because of active educational programs and systematic research activities. Therefore, the involvement of many skilled surgeons will produce accurate clinical outcomes for the procedures. However, because this is not a randomized controlled trial, selection bias might still occur in determining the surgical modality for each subject. To overcome that limitation and secure the surgical and oncologic outcomes from a new, innovative surgical procedure, we are planning a randomized controlled trial for the near future.

Through this study, we wish to confirm that minimally invasive breast surgery can be considered as a standard treatment for women with breast cancer and as a preventive treatment for women with a high risk of pathogenic variants.

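### Endoscopic and robotic surgery are pooled, and the registry subgroup is sized on robotic rates alone, with no planned check that the two techniques have similar outcomes

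*Protocol article*

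**What the plan says.** Statistical analyses names three comparisons: "We have categorized three study sets: Conventional vs. endoscopic, conventional vs. robotic, and conventional vs. endoscopic and robotic". It then describes the registry-trial subgroup, whose purpose is to "compare the surgical and oncologic outcomes between the conventional and minimally invasive (endoscopic and robotic) groups". No robotic-versus-endoscopic contrast is named. ANOVA and Kruskal–Wallis tests are mentioned, but only for continuous variables and only where needed.

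The sample size for that subgroup stands under Pre-specified subgroup analysis. It uses a grade III complication rate of 34.8% in the reference group, 17.1% in the robotic group, a 5-point margin (39.8% under the null hypothesis) and a one-sided unpooled Z test at 0.025. The result is 112 patients matched 1:1, with 80% power and an actual significance level of 0.0265. No endoscopic rate enters.

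The two techniques are defined as separate arms under Study population. Background lists drawbacks specific to endoscopy ("However, ENSM has several limitations: (1) complex devices are needed, (2) the approaches are difficult for endoscopic devices"), and the section on ENSM with IBR adds that "endoscopic techniques for breast surgery have not been widely performed because of the technical challenges with using rigid instruments". The Discussion states the aim as "This study will provide evidence about the surgical outcomes, oncologic outcomes, and patient satisfaction with RNSM and ENSM, compared with CM", and closes with the hope of confirming that "minimally invasive breast surgery can be considered as a standard treatment for women with breast cancer".

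**The concern.** A pooled rate is a weighted average, and here the weights are whatever proportion of endoscopic and robotic patients happens to be enrolled or drawn. Sample size determination gives 2000 patients in total with no split by technique. If outcomes differ between techniques, the pooled comparison estimates a quantity that changes with the mix and describes neither technique.

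In the full cohort, the two separate sets stand beside the pooled one and can reveal a difference. In the registry subgroup they do not, because that comparison is described only in pooled form. It was also sized as if every patient in the non-conventional group were robotic. Two things are at stake: a non-inferiority statement about minimally invasive surgery that one component does not merit, and a loss of power the stated 80% does not reflect. Cost-effectiveness is a secondary endpoint to be judged by surgical method, yet no planned set shows whether the robot differs from the other minimal-access option.

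**Working it through.** **Inputs from Pre-specified subgroup analysis.** Reference rate pC = 0.348; robotic rate pR = 0.171; margin 0.05; null rate 0.348 + 0.05 = 0.398; one-sided 0.025 (critical value 1.96); 112 in total, so n = 56 per group.

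**Assumptions, because the article gives no figures.** The endoscopic share s of the pooled arm is 10%, 25% or 50%. The true endoscopic rate pE is either 0.398 (worse by the whole margin) or 0.348 (equal to conventional).

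**1. The plan's own figure.** Non-inferiority is declared when (T − C − 0.05)/√[C(1 − C)/56 + T(1 − T)/56] < −1.96, where T and C are the observed rates. Summing exact binomial probabilities over all outcomes gives power 0.8004 at a true 17.1% and significance level 0.02645 at a true 39.8%. Both match the article, so 112 is the total and the design is robotic against reference.

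**2. The same test on a pooled arm.** The pooled rate is p = (1 − s) × 0.171 + s × pE. For s = 25% and pE = 0.398: p = 0.75 × 0.171 + 0.25 × 0.398 = 0.22775. As an approximate check, the distance from the null is 0.398 − 0.22775 = 0.17025. The standard error is √[(0.348 × 0.652 + 0.22775 × 0.77225)/56] = 0.0848. So Φ(0.17025/0.0848 − 1.96) = Φ(0.047) ≈ 0.52. Exact summation gives 0.53.

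| Endoscopic share | Pooled rate if pE = 39.8% | Non-inferiority declared | Pooled rate if pE = 34.8% | Power |
|---|---|---|---|---|
| 0% (as sized) | 17.1% | 80% | 17.1% | 80% |
| 10% | 19.4% | 70% | 18.9% | 72% |
| 25% | 22.8% | 53% | 21.5% | 59% |
| 50% | 28.5% | 27% | 26.0% | 37% |

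The pooled null hypothesis is false in each of these rows, so the test is not in error about the mixture. The error would lie in applying its result to endoscopy.

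**3. The full cohort, for contrast.** Take assumed sizes of 1000 conventional, 500 robotic and 500 endoscopic, or 1000/800/200. Let the robotic rate be 17.2% and the endoscopic and conventional rates both 34.8%. In 200,000 simulated studies the pooled test is significant in at least 99%, although endoscopy has no benefit. The separate conventional-versus-endoscopic test rejects in only 5%, so that set would not support a claim for endoscopy. The registry subgroup has no such companion comparison.

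**The case against.** A reader might infer something stronger: that both planned routes, pooling and separate tests against conventional surgery, lead to wrong conclusions. The documents do not support that.

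- The stated aim is each technique against conventional surgery. The two separate sets answer it validly, apart from confounding. No ranking of robotic against endoscopic surgery is announced, and the study is described as exploratory ("we designed a multicenter prospective exploratory cohort study").
- Misreading two separate p-values as a ranking is a real hazard, but its size depends on assumed rates. With 1400/450/150 patients and both techniques at 14% against 20%, robotic is significant and endoscopic is not in 47% of simulated trials. With the article's own 17.2% and 34.8% and the same split, this happens in 0.25%.
- The Background passage concerns devices, access and labour. It does not claim different outcomes, and the section on ENSM calls the technique safe and feasible. Table 2 lists the intervention as the two techniques together, so the grouping looks deliberate.
- The closing sentence of the Discussion is an aspiration and not a decision rule.
- A fuller protocol or analysis plan may contain pairwise contrasts.

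These points stand, and they confine the concern to pooling. They do not remove it. A deliberate grouping still needs a check that the groups are alike. The article itself sizes the subgroup on one pair of groups and describes its analysis with another, and an unseen document does not make those two statements agree.

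**Conclusion.** The concern holds as a point about pooling. Statistical analyses merges the techniques in one study set and in the registry subgroup, names no check of similarity, and conflicts with the robotic-only basis of the subgroup's sample size. Under the article's own design inputs, an endoscopic share of 10% to 50% with a true rate at the null value leaves a 70% to 27% chance that the pooled group is declared non-inferior. If endoscopy merely equals conventional surgery, the stated 80% power falls to between 72% and 37%. These ranges rest on assumed shares and assumed endoscopic rates, and on treating the registry comparisons in the two sections as the same analysis, as their shared name suggests. If endoscopic and robotic rates are in truth the same, pooling does no harm, but nothing in the plan would show it. The separate comparisons with conventional surgery are not faulted here.

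**What to change.** 1. In Statistical analyses, add a robotic-versus-endoscopic difference with a 95% confidence interval for both primary endpoints and for cost-effectiveness. Label it an exploratory heterogeneity check and report it beside the pooled set.
2. State that a conclusion about minimally invasive surgery as a class will be drawn only if each technique's own contrast with conventional surgery supports it. Otherwise the conclusion names the technique.
3. Reconcile Pre-specified subgroup analysis with Statistical analyses. Either the registry subgroup compares robotic with conventional surgery, as it was sized, or its power is restated for the pooled group with an explicit mix and endoscopic rate. As an example, take a 25% share with endoscopy equal to conventional: n = (0.348 × 0.652 + 0.21525 × 0.78475) × (1.96 + 0.8416)²/0.18275² = 93.02, so 94 per group. The same formula gives 57 per group for a purely robotic arm.

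The first two changes cost wording and one further contrast on data already collected. That contrast is non-randomised and open to the same confounding as the others, and its interval will be wide if the endoscopic arm is small. With an assumed 200 per group and a robotic rate of 17.2%, power to detect an endoscopic rate of 34.8%, 25% or 22% is 98%, 48% or 23%. For this reason it should be read as an estimate and not as a test of equality. The published claim may become narrower.

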### Evidence for immediate reconstruction

#### Guidelines and reviews for conventional NSM (CNSM) with IBR

The first NSM was described by Freeman in 1962 but only for RRM [20]. Subcutaneous mastectomy for patients with primary breast cancer was first reported by Hinton et al. in 1984 and showed rates of local recurrence and survival comparable to those with CM [21]. The use of NSM for women with breast cancer has been justified by demonstrating its oncologic and surgical safety. Previous studies confirmed acceptable locoregional recurrence, disease-free survival, and overall survival (OS) rates following NSM [4, 22–27]. The surgical outcomes of NSM, including rates of nipple necrosis and overall postoperative complications, were acceptable in previous reports [4, 22, 23]. The procedure’s advantages in terms of better aesthetic outcomes, improved patient satisfaction, and psychosexual benefits have also been investigated [28–30].

The National Comprehensive Cancer Network (NCCN) guideline comments that SSM showed similar oncologic outcome compared to CM [31]. However, SSM should be performed by an experienced breast surgeon. Similarly, NSM is comparable oncologic outcome to SSM, if cases are appropriately selected. NSM can be performed for any tumor size independent of axillary status, especially for early breast cancer, and for ductal carcinoma in situ and RRM, but having cT4b and cT4c breast cancers with skin involvement or skin edema, and clinical signs of nipple involvement and any R1 resection at the nipple margin should be a contraindication.

#### Guidelines and reviews for ENSM with IBR

Due to aesthetic concerns about the breast, breast surgery has been developed to satisfy both oncologic safety and cosmetic needs [13]. Endoscopic procedures have been used for various breast surgeries, including augmentation, mastectomy, excision, biopsy, capsulectomy, and reconstruction [32].

Endoscopic-assisted breast surgery (EABS) was introduced in the late 1990s to optimize the aesthetic effects by using a minimal incision in an inconspicuous location for benign breast disease or breast cancer [33]. Previous studies reported excellent patient satisfaction on patient-reported questionnaires after ENSM [34–36]. Additionally, endoscopy could offer better visualization with light handle retractions through a small incision and allow similar oncologic outcomes compared to CNSM [13, 37]. Indications and contraindications for EABS are similar to CNSM. Although ENSM is considered a safe and feasible procedure that leaves a relatively inconspicuous incision in patients with breast cancer [38], endoscopic techniques for breast surgery have not been widely performed because of the technical challenges with using rigid instruments [39].

#### Guidelines and reviews for RNSM with IBR

Since the first robotic surgical system was introduced in 2000, robotic surgical systems have spread widely into various surgical fields because of the comfort and ergonomic movement they allow, with magnified and high-resolution vision [40]. Robotic breast surgery has also been developed and investigated by several pioneers to establish clinical evidence for this new technique (Tables 1 and 2) [19, 41–47].

**Table 1 Tab1:** General information on previous studies about RNSM

Study	Year	Study interval	Aim	Design	No. of patients (procedures)	Indication (*n*, %)
Ryu et al. [19]	2020	Nov 2016–Jan 2020	To report the early experience of RNSM with IBR in the KoREa-BSG	Retrospective case series, multicenter	73 (82)	Therapeutic (75, 91.5%)Risk-reducing (7, 8.5%)
Lee et al. [41]	2021	Nov 2016–Jan 2019	To directly compare surgical outcomes between CNSM and RNSM	Retrospective case–control comparison study, single center	CNSM 270 RNSM 41	Therapeutic (34, 83%) Risk-reducing (7, 17.1%)
Toesca et al. [42]	2019	June 2014–Jan 2019	To present and discuss perioperative surgical outcomes and early oncologic follow-up data on consecutive patients undergoing RNSM	Prospective case series, single center	73 (94)	Invasive breast cancer (39, 41.5%) DCIS (21, 223%) Risk-reducing (34, 36.2%)
Sanson et al. [43]	2018	Nov 2015–Jan 2020	To report the feasibility of RNSM with a large series of 138 procedures	Prospective, single center	79 (138)	Prophylactic (75%) Therapeutic (25%)
Lai et al. [44]	2020	July 2011–Sep 2019	To critically compare RNSM vs. CNSM procedures from different aspects (clinical outcomes, patient-reported aesthetic results, and medical costs) in the management of patients with breast cancer	Retrospective case–control comparison study, single center	CNSM 62 RNSM 54	Therapeutic
Houvenaeghel et al. [45]	2021	Nov 2016–Mar 2020	To compare RNSM and CNSM in terms of the breast complication rate (main objective) and hospital stay, duration of surgery, cost evaluation, and patient satisfaction (secondary objectives)	Prospective case–control comparison study, single center	CNSM 142 RNSM 87	Primary (70, 80.5%) Local recurrence (10, 11.5%) Prophylactic (7, 8.0%)
Loh et al. [46]	2020	April 2018–Jan 2020	To report the use of RNSM in patients with breast cancer and analyze the learning curve of one surgeon in a single medical center	Retrospective single center	78 (85)	Therapeutic
Kuo et al. [47]	2019	N/A	To report the combination of robotic mastectomy and immediate microsurgical free-flap reconstruction and exploit its oncologic and aesthetic advantages	Case series, single center	3	Therapeutic

*CNSM* conventional nipple-sparing mastectomy, *IBR* immediate breast reconstruction, *KoREa-BSG* Korea Robot-Endoscopy Minimal Access Breast Surgery Study Group, *RNSM* robotic nipple-sparing mastectomy

**Table 2 Tab2:** Summary of ongoing studies of RNSM

Identifier	Sample size	Randomization	Indication	Intervention	Postoperative outcomes	Oncologic outcomes	PRO	Country of origin
NCT04585074 (current study)	2000	No	Women with breast cancer High-risk women	RNSM + ENSM CNSM	Yes	Yes	Yes	South Korea
NCT04108117	300	No	Women with breast cancer High-risk women	RNSM CNSM	Yes	Yes	No	South Korea
NCT03440398	82	Yes	Women with breast cancer High-risk women	RNSM CNSM	Yes	Yes	Yes	Italy
NCT03892980	145	No	High-risk women	RNSM	Yes	No	No	United States
NCT04537312	20	No	Women with breast cancer High-risk women	RNSM	Yes	No	Yes	United States
NCT04457167	480	No	Women with breast cancer High-risk women	RNSM CNSM	Yes	No	No	France
NCT04151368	30	No	Women with breast cancer High-risk women	RNSM	Yes	Yes	Yes	Canada
NCT04037852	180	No	Women with breast cancer	RNSM CNSM or ENSM	Yes	Yes	Yes	Taiwan

*CNSM* conventional nipple-sparing mastectomy, *ENSM* endoscopic nipple-sparing mastectomy, *PRO* Patient-reported outcome, *RNSM* robot-assisted nipple-sparing mastectomy

No intraoperative or postoperative mortality caused by RNSM has been reported and only one case of open conversion experienced in the literature [16]. The rates of postoperative complications have primarily been acceptable [16, 41, 42, 48]. In terms of oncologic safety, a few reports have indicated a favorable incidence of margin positivity and no locoregional recurrence within short-term follow-up [42, 47, 48]. The innovative robotic technique in breast surgery has been presented as a safe and feasible surgical procedure that is not inferior to the conventional methods in terms of early oncological outcomes [42].

As RNSM attracted attention and became the focus of more research, standardized RNSM guidelines were developed by a representative panel of 10 international experts in 2019 [49]. Previous studies have suggested that an indication and contraindication for RNSM is similar to CNSM [48–50].

